## REVISION HISTORY

| Revision # | Version Date | Summary of Changes | Consent Change? |
|------------|--------------|--------------------|-----------------|
|            |              |                    |                 |
|            |              |                    |                 |
|            |              |                    |                 |
|            |              |                    |                 |
|            |              |                    |                 |
|            |              |                    |                 |
|            |              |                    |                 |

## **ABBREVIATIONS/DEFINITIONS**

## **1.0 Objectives**

- 1.1 Purpose: This project will evaluate the use of a health systems intervention, against a background of a mass media campaign, designed to improve the appropriate use of aspirin for the prevention of heart attack and stroke in a high-risk adult population. Using the population of the state of Minnesota as a base, it will develop methods to improve aspirin use at the community level.

## **2.0 Background**

- 2.1 Significance of Research Question/Purpose: Although significant progress in the reduction of acute myocardial infarction and stroke is apparent, these cardiovascular disorders continue as the leading causes of morbidity and mortality. In recent years, and in the context of the positive results from large randomized clinical trials, there is growing consensus that aspirin, when appropriately used, reduces cardiovascular morbidity in men and women. While use of aspirin to prevent a first heart attack or stroke is beneficial, only about 30-40% of the eligible Minnesota population uses aspirin for the primary prevention of heart attack or stroke. In contrast, 75-85% of individuals who should use aspirin for secondary prevention do so.
- 2.2 Preliminary Data: In 2012, a pilot study was initiated to test the intervention components and evaluation procedures in the community of Hibbing, MN. Baseline, 4-month and 18-month follow-up telephone surveys of randomly selected adults (men aged 45-79 and women 55-79) resulted in participation rates of 60%. From baseline to follow-up, aspirin use for primary prevention increased significantly from 37% to 52%.
- 2.3 Existing Literature: Seven major prospective randomized placebo controlled clinical trials over 25 years have examined the efficacy and risk of aspirin use to prevent a first heart attack or stroke. In the United States, the Physicians Health Study and Women's Health Study evaluated over 60,000 individuals. The 2016 U.S. Preventive Services Task Force (USPSTF) recommendation endorses the use of aspirin for the primary prevention of hearts attacks and strokes in men and women ages 50-59 with a 10% or greater 10-year CVD risk (B recommendation) and men and women ages 60-69 with a 10% or greater 10-year CVD risk (C recommendation).

## **3.0 Study Endpoints/Events/Outcomes**

- 3.1 Primary Endpoint/Event/Outcome: Self-reported aspirin use for CVD primary prevention in random samples of Minnesota and Upper Midwest men ages 45-79 and women ages 55-79.
- 3.2 Secondary Endpoint(s)/Event(s)/Outcome(s): N/A

#### **4.0 Study Intervention(s)/Investigational Agent(s)**

4.1 Description: The study intervention consists of two educational components: one aimed at increasing public awareness of effective heart attack and stroke prevention, through a variety of media and public relations outlets; and, a second aimed at integrating USPSTF recommendations as a part of a health system's quality improvement (QI) initiative, and providing the education and tools to facilitate the appropriate recommendation of primary prevention aspirin use to patients. The desired action on the part of the public is for men and women in the targeted age groups to consult their health professional(s) to ask if they should take aspirin. The action desired on the part of health professionals is for them to evaluate their patients immediately about the use of aspirin for cardiovascular disease prevention and to recommend it to those individuals for whom it is appropriate.

4.2 Drug/Device Handling: N/A

4.3 Biosafety: N/A

4.4 Stem Cells: N/A

#### **5.0 Procedures Involved**

5.1 Study Design: The study design consists of a group-randomized trial (GRT) to evaluate two interventions, a media communications campaign and a health system approach to enhance the effectiveness of care providers to improve appropriate aspirin use among men and women per the USPSTF guidelines. GRTs are characterized by the random assignment of identifiable units rather than individuals to study conditions, with measurements taken on the members of those groups to assess the impact of the intervention. In this study, the groups are 24 defined geographic areas in the State of Minnesota. The independent effects of the media intervention and the joint effects of media plus a health system approach will be evaluated. At baseline, all 24 geographic areas will receive the media communication campaign and only 12 geographic areas will receive the health system intervention. After 2 years, the remaining 12 geographic areas will receive the health system intervention with the media campaign continuing across all 24 areas. To control for secular trends of aspirin use, 4 surrounding states will be evaluated (Iowa, North Dakota, South Dakota and Wisconsin).

- 5.2 Study Procedures: The primary endpoint of this study, appropriate aspirin use for primary CVD prevention, will be collected by telephone survey in randomly selected individuals ages 45-79. The group-randomized design includes 100 participants in each of 24 selected geographic areas for each survey. 1200 participants will be surveyed across the 4 surrounding states. In addition to verbal consent, the survey will contain demographic questions, questions on aspirin use, CVD status, physician contacts, risk factors, media exposure and other items relevant to understanding program effects. The telephone survey has been administered at baseline (year 2015) and at year 3 (2017). It will also be administered in year 5 (2019).

To assure minority representation in the surveys, 800 in-person surveys of age appropriate individuals from minority groups were surveyed respectively at baseline (year 2015) and at year 3 (2017). The in-person survey of 800 age appropriate individuals from minority groups will also be surveyed in year 5 (2019).

- 5.3 Study Duration: Individual participants spend approximately 10 minutes answering the questions in the telephone survey and the in-person survey.
- The duration anticipated to enroll all study participants is through 2020.
  - The duration anticipated to complete all study procedures, including data analysis is 2021.

5.4 Individually Identifiable Health Information: N/A

5.5 Use of radiation: N/A

5.6 Use of Center for Magnetic Resonance Research: N/A

## **6.0 Data and Specimen Banking N/A**

## **7.0 Sharing of Results with Participants N/A**

## **8.0 Study Population**

- 8.1 Inclusion Criteria: Men and women ages 45-79 years living in Minnesota, Iowa, North Dakota, South Dakota, and Wisconsin. Men and women ages 45-79 from minority groups living in Minnesota.

8.2 Exclusion Criteria: N/A

- 8.3 Screening: Individuals will be assessed for eligibility by asking the individual for the year they were born and for their state of residence.

## 9.0 Vulnerable Populations

### 9.1 Vulnerable Populations:

- ☐ Children
- ☐ Pregnant women/Fetuses/Neonates
- ☐ Prisoners
- ☐ Adults lacking capacity to consent and/or adults with diminished capacity to consent, including, but not limited to, those with acute medical conditions, psychiatric disorders, neurologic disorders, developmental disorders, and behavioral disorders
- ☐ Approached for participation in research during a stressful situation such as emergency room setting, childbirth (labor), etc.
- ☐ Disadvantaged in the distribution of social goods and services such as income, housing, or healthcare
- ☐ Serious health condition for which there are no satisfactory standard treatments
- ☐ Fear of negative consequences for not participating in the research (e.g. institutionalization, deportation, disclosure of stigmatizing behavior)
- ☐ Any other circumstance/dynamic that could increase vulnerability to coercion or exploitation that might influence consent to research or decision to continue in research
- ☐ Undervalued or disenfranchised social group
- ☐ Members of the military
- ☒ Non-English speakers
- ☐ Those unable to read (illiterate)
- ☐ Employees of the researcher
- ☐ Students of the researcher
- ☐ None of the above

- 9.2 Additional Safeguards: As part of the NIH guidelines for NIH-funded grants, minority populations need to be represented in the study research. In this study, we have translated the in-person survey into Spanish to allow for the recruitment of predominantly Spanish-speaking individuals. The interviewers are also Spanish-speakers and have been appropriately trained to gather information from these individuals. The survey questions are minimally invasive and are believed to pose low risk to this community.

## **10.0 Local Number of Participants**

### *10.1* Local Number of Participants to be Consented:

The number of subjects approved to be enrolled for this study is 14040.

## **11.0 Local Recruitment Methods**

*11.1* Recruitment Process: The UMN Minnesota Center for Survey Research (MCSR) will mail a pre-telephone survey cover letter to random households across the 24 geographic areas in Minnesota and across the 4 adjacent States, who have been identified as potentially having a man or woman between the ages of 45 and 79. This pre-telephone survey letter will introduce the study and inform individuals that they will be receiving a phone call to conduct a 5-10 minute one-time survey. A week later, MCSR will call these households and screen the recipients for their age-eligibility and interest in participating in the telephone survey.

A community-based organization serving minority populations conducts the in-person interviews at community events or other locations serving these populations.

*11.2* Identification of Potential Participants: Publically available lists of landline households are used to contact potential participants for the telephone surveys. For the in person surveys, tables are set up at community events with flyers that indicate the age specifications for the study.

*11.3* Recruitment Materials: A pre-survey letter is used in advance of the telephone survey to inform potential participants of the survey call. Flyers at community events are used to recruit individuals from minority groups at community events.

*11.4* Payment: No payment is provided to telephone participants. A \$10 gift card is provided to individuals from minority groups participating in the in-person interviews.

## **12.0 Withdrawal of Participants**

*12.1* Withdrawal Circumstances: N/A

*12.2* Withdrawal Procedures: N/A

### **13.0 Risks to Participants**

*13.1* Foreseeable Risks: The 10 minute participation in a one-time telephone survey or in-person survey of CVD health questions and aspirin use is believed to pose minimal risk.

*13.2* Reproduction Risks: N/A

*13.3* Risks to Others: N/A

### **14.0 Potential Benefits to Participants**

*14.1* Potential Benefits: N/A

### **15.0 Statistical Considerations**

*15.1* Data Analysis Plan: The design is a member-cross-section Group Randomized Trial as respondents at baseline and at follow-up will not be restricted to be the same persons. We will use a mixed-model logistic regression analysis of 2 and 4-year follow-up aspirin use data, adjusting for baseline mean levels and covariates.

*15.2* Power Analysis: For 100 members per geographic area, a two-tailed Type 1 error rate of 5% will have 85% power for an absolute intervention effect of 8/1%, e.g., 30% vs. 38.1%; at 80% power the detectable difference would be 7.6%.

*15.3* Statistical Analysis: The mixed-model logistic regression analyses will be fit using SAS PROC GLIMMIX specifying a logit link and a binomial error. We will assess the null hypothesis of no joint intervention effect by testing the randomization condition (health system vs. media comparison) against the area-level (cluster) error term. Surveys will balance the numbers of men and women so as to allow the most sensitive analyses with gender strata.

*15.4* Data Integrity: Trained interviewers are used for both the telephone and in-person surveys.

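### The stated 85% power counts all 100 interviews per area, although some respondents cannot contribute to the primary endpoint, so it is too high by an amount the protocol does not let one fix

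*Protocol*

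**What the plan says.** - **Endpoint (3.1):** "Self-reported aspirin use for CVD primary prevention in random samples of Minnesota and Upper Midwest men ages 45-79 and women ages 55-79".
- **Inclusion (8.1):** "Men and women ages 45-79 years living in Minnesota, Iowa, North Dakota, South Dakota, and Wisconsin". Section 8.2 lists no exclusions.
- **Screening (8.3):** eligibility is assessed by "asking the individual for the year they were born and for their state of residence". CVD status is a question inside the interview (5.2), so people with CVD are already among those counted.
- **Survey size (5.2):** 100 participants in each of 24 areas per wave, sampled from ages 45-79. This section attaches the endpoint to that whole age range.
- **Power (15.2):** "For 100 members per geographic area, a two-tailed Type 1 error rate of 5% will have 85% power". The example behind this figure is a rise from 30% to 38.1%; the difference is printed as 8/1%, evidently a slip for 8.1 points. A difference of 7.6 points is given for 80% power. No intracluster correlation (ICC) and no eligible share is given.
- **Sex balance (15.3):** "Surveys will balance the numbers of men and women so as to allow the most sensitive analyses with gender strata".

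**The concern.** The power statement and the endpoint use different denominators. A respondent with established CVD cannot be a primary-prevention user or non-user, and a woman of 50 is outside the ages in 3.1, yet each fills one of the 100 places. The number per area that informs the primary comparison is then below 100, while 15.2 makes no allowance for this.

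At stake is how a null result is read: a trial believed to have 85% power for 8.1 points would be credited with ruling out effects that it was less able to detect. The sex strata in 15.3 are also affected. If women 45-54 do not count, equal numbers of interviews leave fewer eligible women than men.

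**Working it through.** **Inputs from the protocol.** Two-sided 5% test; 30% vs 38.1%; 24 areas, 12 with and 12 without the health system intervention until year 2 (5.1); 100 per area; test against the area-level error (15.3), hence 22 df for an unadjusted comparison.

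**Inputs assumed.** The ICC is back-solved from 15.2. Half of the interviews are with women (15.3). Ages are uniform over 45-79, so 10 of 35 years, or 29% of women, are aged 45-54. The CVD share is 10-25%. The protocol gives none of the ICC, the age mix or the CVD share.

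**Step 1: reproduce 15.2.** With m respondents per area,

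SE² = [p1(1−p1) + p2(1−p2)] × [1 + (m−1)ICC] / (12m), and power ≈ P(T22 < difference/SE − 2.074).

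- 85% power at 0.081 needs SE = 0.081/(2.074 + 1.061) = 0.02583.
- Without clustering, SE² = (0.2100 + 0.2358)/1200 = 0.0003715.
- Implied design effect = 0.02583²/0.0003715 = 1.796, so ICC = 0.796/99 = 0.0080.
- With that ICC, the difference detectable at 80% power is 7.56 points, against 7.6 stated.

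The two figures in 15.2 therefore agree with each other at m = 100. Other variance formulas and degrees of freedom give an ICC between 0.0078 and 0.0110 and change the powers below by no more than about 1.5 points.

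**Step 2: eligible respondents per area.** m = [50 + 50(1 − w)] × (1 − c), where w is the share of women aged 45-54 treated as outside the endpoint and c is the CVD share.

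**Step 3: power for 30% vs 38.1% at ICC 0.0080.**

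| Who is lost | m | Power |
|---|---|---|
| Nobody (15.2) | 100 | 85% |
| CVD only, 10% | 90 | 83% |
| CVD only, 25% | 75 | 79% |
| Women 45-54 only | 86 | 82% |
| Both, CVD 10% | 77 | 79% |
| Both, CVD 15% | 73 | 78% |
| Both, CVD 20% | 69 | 76% |
| Both, CVD 25% | 64 | 74.5% |

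At m = 68, power is 76% and the detectable differences are 9.1 points (85% power) and 8.5 points (80% power), instead of 8.1 and 7.6.

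**Step 4: sex strata.** If women 45-54 do not count, 50 men and 50 × 25/35 = 36 women per area remain before CVD is removed.

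**Step 5: could 100 mean eligible respondents?** Section 10.1 approves 14,040 participants. Taking three equal waves gives 4,680 per wave. Subtracting the 1,200 neighbouring-state and 800 in-person interviews (5.2) leaves 2,680, or about 112 per area. Reaching 100 eligible would then allow at most about 10% ineligible (100/112 = 0.895). No section describes an eligible quota or oversampling.

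**The case against.** **The women aged 45-54 may not be lost.** Section 3.1 describes the random samples themselves as men 45-79 and women 55-79, the pilot in 2.2 sampled exactly those ages, and 11.1 screens for age-eligibility, so 45-79 may be shorthand for the overall range. Conversely, 5.2 places the endpoint in everyone aged 45-79, and then these women count. Either reading leaves only the CVD loss. This stands: the sections contradict each other, and it is not established that these interviews are wasted.

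**The back-solved ICC assumes an unadjusted single-wave comparison.** Section 15.1 adjusts for baseline means and covariates. If the 85% already includes that gain, the underlying ICC is larger and power is less sensitive to m. As an illustration, an ICC of 0.015 or 0.02, with a fixed variance reduction chosen to give 85% at m = 100, gives about 79% or 80% at m = 68 instead of 76%. This also stands, although fewer eligible respondents at baseline would weaken the adjustment too.

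**Stronger readings the protocol does not support.** A reader might infer that true power is some particular figure in the 70s. That needs an ICC, an age mix and a CVD share that the protocol does not give. A reader might also fault the 30% comparison rate, but it is offered as an example and lies within the 30-40% of 2.1. Nor does anything show that respondents with CVD would enter the primary analysis: CVD status is recorded, so they can be set aside there.

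None of this restores 85%. With 100 interviews per area, no exclusions and no CVD screen, any non-zero CVD share leaves fewer than 100 for a primary-prevention endpoint.

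**Conclusion.** The point holds as a mismatch of populations that makes the power in 15.2 too high. It is not an arithmetic error, since the figures in 15.2 agree with each other at 100 per area. The direction follows from the text; the size is conditional. With the implied ICC of about 0.008, an unadjusted test on 22 df and the assumed shares above, the shortfall from 85% is about 2 to 6 points if only respondents with CVD are lost, about 3 if only women 45-54 are lost, and about 6 to 10 if both are. It is smaller if 15.2 already credits baseline adjustment. The protocol does not allow one true value to be stated.

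**What to change.** 1. **Restate 15.2** on endpoint-eligible respondents per area. The 2015 and 2017 surveys were complete at this protocol version, and the survey records sex, birth year, CVD status and aspirin use. Eligible counts, the comparison rate and the ICC can therefore be taken from the data in hand. State the ICC, and say whether baseline adjustment is credited. The cost is a recalculation and a less favourable power statement.
2. **Reconcile 3.1, 5.2, 8.1 and 8.3**, stating in particular whether women 45-54 belong to the endpoint population. The cost is a text change.
3. **Optionally, for 2019 only**, add sex and CVD history to the screener, so that the 100 per area and the sex balance count eligible respondents. The cost is two questions and extra screening calls, with no increase in the target number of interviews. This cannot raise eligible numbers in 2015 or 2017. On the schedule in 5.1 the comparison areas receive the health system intervention after 2 years, so it would not strengthen the 2017 comparison, the follow-up wave closest to the end of the unmixed contrast.

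### Section 15.3 names a null of no joint effect, but with media in all 24 areas the randomised contrast measures only the added health-system effect at 2 years, and early versus delayed introduction at 4 years

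*Protocol*

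**What the plan says.** Protocol section 5.1 describes the study as "a group-randomized trial (GRT) to evaluate two interventions, a media communications campaign and a health system approach" and announces two targets: "The independent effects of the media intervention and the joint effects of media plus a health system approach will be evaluated". The allocation follows in the same section: "At baseline, all 24 geographic areas will receive the media communication campaign and only 12 geographic areas will receive the health system intervention". It then changes: "After 2 years, the remaining 12 geographic areas will receive the health system intervention with the media campaign continuing across all 24 areas". The areas outside the intervention are introduced by "To control for secular trends of aspirin use, 4 surrounding states will be evaluated (Iowa, North Dakota, South Dakota and Wisconsin".

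Section 15.3 states the hypothesis and its test together: "We will assess the null hypothesis of no joint intervention effect by testing the randomization condition (health system vs. media comparison". The comparison is made against area-level error. Section 15.1 applies the mixed logistic model to the 2-year and 4-year follow-up data.

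Section 1.1 puts the purpose differently. The project will "evaluate the use of a health systems intervention, against a background of a mass media campaign".

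**The concern.** The hypothesis in 15.3 and the test assigned to it concern different quantities. A joint effect is media plus health system compared with neither. The randomised condition compares media plus health system with media. Section 5.1 adds to the difficulty by presenting the media effect and the joint effect as things a group-randomised trial evaluates, although no randomised area is without media.

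Two conclusions are at stake. First, a non-significant result read against the null as written would be taken as no evidence that the combined programme works, when the test is blind to the media part of it. Second, a reader of 5.1 could credit a media or joint effect with the protection of randomisation, which it does not have.

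**Working it through.** **Inputs.** From section 5.1: media in 24 of 24 areas throughout; health system in 12 of 24 for the first 2 years and in all 24 afterwards; four surrounding states outside the randomised set. From 15.2: 100 respondents per area, two-sided 5%, 8.1 points (30% vs 38.1%, printed with a slash) at 85% power and 7.6 points at 80%.

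**The plan's own power figure.** The detectable differences in 15.2 belong to a 12 vs 12 comparison of areas. With 12 × 100 = 1,200 per arm and no clustering, power for 30% vs 38.1% would be 98.7%, so a design effect must be included. The protocol gives no intracluster correlation (ICC). Using variance [p1(1−p1) + p2(1−p2)]/1,200 × [1 + 99 × ICC] and a noncentral t on 22 df, the ICC that returns 85% at 8.1 points is 0.0080 (design effect 1.80). With that value the difference detectable at 80% is 7.56 points, which rounds to the stated 7.6. The two figures agree with each other, and both refer to the randomised comparison. The 8.1 points is therefore an increment over media, not a joint effect.

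**What each comparison identifies.** Let S be the secular change since baseline, M the media effect, and H the effect of the health system added to media. Any interaction with media is inside H by definition. Changes from baseline at 2 years are:

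| Group | Change |
|---|---|
| 12 areas, media + health system | S + M + H |
| 12 areas, media only | S + M |
| Surrounding states, taken as unexposed | S |

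- Randomised contrast: (S + M + H) − (S + M) = H. M cancels, and it cancels on the logit scale as well if the terms are read as log-odds.
- Media effect: (S + M) − S = M, which needs the surrounding states.
- Joint effect: (S + M + H) − S = M + H, which also needs the surrounding states.
- Before-after change within Minnesota media-only areas: S + M, which cannot separate media from trend.

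**At 4 years.** Both sets of 12 areas have media and the health system. Write H_early and H_delayed for the health-system effect after the longer and the shorter exposure. The randomised contrast is (S + M + H_early) − (S + M + H_delayed) = H_early − H_delayed. This is early versus delayed introduction. It is neither H nor M + H.

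**Illustration (M and H are assumed, in percentage points).**

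| M | H | Randomised contrast at 2 years | Joint effect |
|---|---|---|---|
| 5 | 0 | 0 | 5 |
| 5 | 8.1 | 8.1 | 13.1 |

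If M = 5 and the health-system effect has reached 8.1 in both sets of areas by year 4, the 4-year contrast is 8.1 − 8.1 = 0 while the joint effect is 5 + 8.1 = 13.1.

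**The case against.** The best defence is that the protocol discloses the real comparison. The parenthesis in 15.3 names health system against media, 1.1 sets the health-system question on a media background, and 5.1 says openly that every area gets media. The test, its area-level error term and the sample size are all suitable for the incremental question. The protocol also supplies a comparator for media in the surrounding states, and the details of that analysis may lie in a statistical analysis plan that is not at hand.

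Most of this stands, and it limits the point to labelling and inference. It does not remove it. The sentence in 15.3 states a hypothesis and a test that do not match, and an analysis plan cannot make media differ between arms that both receive it.

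Some stronger readings are tempting but unsupported:

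- **That the randomised test is invalid.** It is a proper test of the added health-system effect at 2 years.
- **That results will be misreported.** The protocol does not say how results will be reported; the wording only permits the wrong conclusion.
- **That out-of-state interviews would be analysed as independent.** No such analysis is proposed, and the only error term named is at area level.
- **That the lack of a stated model for the surrounding states is itself an error.** That detail can be left to an analysis plan.

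**Conclusion.** Section 15.3 is wrong as written, and the framing in 5.1 promises more than the randomisation can deliver. The randomised contrast identifies H at 2 years and early versus delayed introduction at 4 years. The discrepancy between the 2-year contrast and the named joint effect is exactly M, whatever M is; the protocol gives no value for it. Failing to reject is uninformative about media and about the combined programme. Rejecting at 2 years supports an added health-system effect and nothing about media.

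The algebra assumes that the media campaign is delivered to both arms as 5.1 describes. Recovering M or M + H further assumes that the surrounding states are free of the campaign and share Minnesota's secular trend, and randomisation guarantees neither. A reader might infer that the plan's numbers must change too. They need not: the 15.2 figures remain usable once they are understood as an increment over media.

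**What to change.** In 15.3, replace the null for the 2-year survey with: no added effect of the health-system intervention over media alone. Label the 4-year contrast separately as early versus delayed introduction of the health system. Using the 2-year wording for both surveys would mislabel the later one.

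In 5.1, state that these two contrasts are the only randomised ones, and that the media and joint effects are non-randomised comparisons with the surrounding states, carrying no randomised or confirmatory claim. This brings 5.1 and 15.3 into line with 1.1.

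The cost is a few sentences and a weaker claim for media. No new data are required, and the test and the sample size are unchanged. The relabelling follows from the allocation alone, so it does not depend on any survey result.
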